# Effects of transcranial LED therapy on the cognitive rehabilitation for diffuse axonal injury due to severe acute traumatic brain injury: study protocol for a randomized controlled trial

**DOI:** 10.1186/s13063-018-2632-5

**Published:** 2018-04-24

**Keywords:** Brain injuries, Diffuse axonal injury, Low-level light therapy, Neurologic manifestations, Quality of life, Brain diseases, Trauma, Central nervous system diseases, Nervous system diseases, Craniocerebral trauma

## Abstract

**Background:**

Photobiomodulation describes the use of red or near-infrared light to stimulate or regenerate tissue. It was discovered that near-infrared wavelengths (800–900 nm) and red (600 nm) light-emitting diodes (LED) are able to penetrate through the scalp and skull and have the potential to improve the subnormal cellular activity of compromised brain tissue. Different experimental and clinical studies were performed to test LED therapy for traumatic brain injury (TBI) with promising results. One of the proposals of this present study is to develop different approaches to maximize the positive effects of this therapy and improve the quality of life of TBI patients.

**Methods/design:**

This is a double-blinded, randomized, controlled trial of patients with diffuse axonal injury (DAI) due to a severe TBI in an acute stage (less than 8 h). Thirty two patients will be randomized to active coil helmet and inactive coil (sham) groups in a 1:1 ratio. The protocol includes 18 sessions of transcranial LED stimulation (627 nm, 70 mW/cm^2^, 10 J/cm^2^) at four points of the frontal and parietal regions for 30 s each, totaling 120 s, three times per week for 6 weeks, lasting 30 min. Patients will be evaluated with the Glasgow Outcome Scale Extended (GOSE) before stimulation and 1, 3, and 6 months after the first stimulation. The study hypotheses are as follows: (1) transcranial LED therapy (TCLT) will improve the cognitive function of DAI patients and (2) TCLT will promote beneficial hemodynamic changes in cerebral circulation.

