### Study purpose and objectives

The purposes of this study are to evaluate early and delayed effects of transcranial light-emitting diode (LED) therapy (TCLT) and determine whether this therapy is effective for the cognitive rehabilitation of DAI patients after TBI.

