### Primary outcome measures

The primary hypothesis is that there will be evidence of improvement in functional outcome measured by the Glasgow Outcome Scale Extended (GOSE) after stimulation in comparison to the placebo group at 3 months.

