### Outcome variables

#### Primary

Improvement in functional outcome measured by the GOSE after 3 months of the first stimulation [57].

The authors decided for an approach based on dichotomizing the GOSE (favorable vs unfavorable response). For analysis of outcomes at 3 months, the authors pre-specified death, persistent vegetative state, and severe disability on the GOSE as unfavorable outcomes. Analyzing the GOSE on a binary outcome measure reflects success or failure more plainly, which simplifies the matter of assigning a score to a patient too cognitively impaired to be tested. Moreover, describing the study on this way eases the interpretation for clinical significance [61]. Many studies in TBI [61–63] analyze and prefer to interpret this scale in its dichotomized form.

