## Discussion

This study protocol is designed to focus on investigating the neuromodulation role of transcranial LED therapy (TCLT) for patients who are victims of severe traumatic brain injury (TBI) with diffuse axonal injury. The objective of the study is to verify the hypothesis that this therapy presents pro-cognitive effects for rehabilitation.

Different studies have emerged to prove the positive effect of TCTL for neuropsychological diseases. After these results, some studies, most of which are case series [66–68], have approached the effects of this treatment for TBI with interesting results.

No specific clinical trials on intervention in the acute stage of TBI were found, which justifies the need for an investigation of the efficacy and effectiveness of TCLT. Considering the global impact of TBI on public health policies, the idea of a non-invasive therapy which helps in neurorehabilitation has an interesting appeal.

The first animal model described with TBI treated with TCLT (808-nm NIR/red LED) was performed with mice. Mice were submitted to only one TCLT section for 4 h. An important reduction (about 90%) of post-injury area size was noticed. Neurological severity scores were also significantly lower at 28 days for laser-treated mice [66]. A different approach with a 6-min daily TCLT session for 10 days reverted deficits in working memory tests of mice [67].

A two-case study with TCLT performed to improve cognitive function in chronic mild TBI patients found improvements in verbal learning, executive function, and memory [68]. With a higher number of patients with chronic mild TBI, the same author published positive results for 11 patients submitted to 18 outpatient sessions, starting at 10 months to 8 years post-TBI. In this study, each LED cluster head (5.35-cm diameter, 500 mW, 22.2 mW/cm^2^) was applied for 10 min to each 11 scalp placement (13 J/cm^2^). They evidenced improvements in executive function as well as sleep and fewer post-traumatic stress disorders [69].

Increasing the number of sessions, another series of two patients submitted to 18 red/NIR TCLT treatments (500 mW, 22.2 mW/cm^2^, 22.48 cm^2^ per treatment area) in chronic TBI patients (who began TCLT at 10 months to 8 years post-TBI) showed improvements in cognition (mainly executive function and verbal memory) [68].

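### The framing text says the trial tests cognition, but the primary hypothesis, endpoint, sample size and test all concern functional outcome on a two-way GOSE, and no cognitive test is listed

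*Protocol article*

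**What the plan says.** The protocol article states its question in two ways.

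**As cognition.** The title speaks of cognitive rehabilitation, and the abstract's Discussion repeats this. Hypothesis (1) in the abstract's Methods/design is that "transcranial LED therapy (TCLT) will improve the cognitive function of DAI patients". The section Study purpose and objectives aims to "determine whether this therapy is effective for the cognitive rehabilitation of DAI patients after TBI". The main Discussion gives the objective as to "verify the hypothesis that this therapy presents pro-cognitive effects for rehabilitation".

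**As functional outcome.** The section Primary outcome measures gives the primary hypothesis: "there will be evidence of improvement in functional outcome measured by the Glasgow Outcome Scale Extended (GOSE"), compared with placebo at 3 months. Under Outcome variables, the primary endpoint is "Improvement in functional outcome measured by the GOSE after 3 months of the first stimulation". It is analyzed as two classes, for which the authors "pre-specified death, persistent vegetative state, and severe disability on the GOSE as unfavorable outcomes". One reason given for the two-way split is that it "simplifies the matter of assigning a score to a patient too cognitively impaired to be tested".

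The secondary outcomes are GOSE at 1 and 6 months, the Marshall, Adams and Gennarelli grades, and transcranial Doppler velocities and indices.

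**The concern.** The reader is told that the trial asks about cognition, but the single primary test answers a question about global disability. The two can come apart in this population. Patients are enrolled in coma with a Glasgow Coma Scale score of 8 or less, and the Background names diffuse axonal injury as the leading cause of persistent vegetative state and severe disability after brain injury. Many of the ways to move from unfavorable to favorable need not involve a specific cognitive effect.

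What is at stake is the conclusion that may be drawn. Under the present framing, a significant GOSE difference could be taken as evidence of cognitive rehabilitation, and a null difference as evidence that the therapy does not help cognition. Neither inference follows from the planned data.

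**Working it through.** This is mainly a matter of setting the sections side by side. The one stated figure is reproduced first, to establish which outcome the trial was sized for.

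**1. What the sample size is for.** Sample size calculation bases the number on the favorable/unfavorable proportions, with a chi-square test, an effect size of 0.5, alpha of 5% and power of 80%. Two-sided testing is assumed, since the article does not state it. Reading the 0.5 as the chi-square effect size w, with 1 degree of freedom:

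N = (1.960 + 0.842)² / 0.5² = 7.85 / 0.25 = 31.4, rounded up to 32.

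The noncentral chi-square power at N = 32 is 80.7%. The stated 32 (16 per arm) is therefore reproduced for the two-way GOSE. No input relates to a cognitive endpoint. (The article labels the 0.5 as Cohen's D, and a two-means calculation with d = 0.5 would need 63 per arm. That is a separate labelling matter and does not affect this point.)

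**2. Each place where a cognitive measure would appear.**

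| Section | What is listed | Cognitive test? |
|---|---|---|
| Primary outcome measures; Outcome variables, Primary | GOSE at 3 months, two classes | No |
| Secondary outcome measures; Outcome variables, Secondary | GOSE at 1 and 6 months; Marshall, Adams, Gennarelli; Doppler | No |
| Instruments of evaluation | GOSE, Adams, Marshall, Gennarelli, Abbreviated Injury Scale | No |
| Cerebral blood flow evaluation | Transcranial Doppler | No |
| Baseline measures | Demographics, trauma, admission and hospital-stay data, dysautonomia | No |
| Fig. 2 caption | Baseline data, GOSE, Doppler, CT; the same instruments repeated at follow-up | No |
| Statistical analysis | Chi-square for GOSE, Mann-Whitney for the grades, t test for Doppler | No |

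Neuropsychologists are mentioned once, under Randomization and blinding, as blinded staff. No test is attached to them.

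**3. Which hypotheses have an endpoint.**

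| Hypothesis | Matching endpoint |
|---|---|
| Functional outcome on GOSE (Primary outcome measures) | Yes, with sample size and test |
| Hemodynamic change (abstract, hypothesis 2) | Yes, Doppler |
| Cognitive function (abstract, hypothesis 1; purpose; Discussion) | None listed |

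**4. What the cut can and cannot register.** GOSE has eight levels. Taking both severe-disability levels as unfavorable, four levels fall on each side, with the cut between the fourth and the fifth. There are 8 − 1 = 7 one-level improvements. Exactly 1 crosses the cut and changes the primary outcome; the other 6 do not. This counts steps on the scale, not patients. It follows that:

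- a patient who survives, regains consciousness or becomes physically independent can cross the cut whether or not the therapy acted on cognition;
- a cognitive gain that moves a patient within the favorable or within the unfavorable class, or that changes no GOSE level at all, leaves the primary outcome as it was.

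GOSE at 1 and 6 months is analyzed in the same two-way form, so it does not close the gap. The imaging and clinical grades and the Doppler values describe injury severity and blood flow, not cognition.

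**The case against.** The strongest reply is that the operative hypothesis is already right. Primary outcome measures states it as functional outcome on GOSE at 3 months, and the endpoint, sample size and test all follow from it. This stands: the mismatch lies between the framing text and the body, not within the primary analysis.

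A second reply is that GOSE is not unrelated to cognition. The Background cites a definition of disability that includes poor cognitive and mental health, and calls the cognitive sequelae of this injury disability symptoms. The authors also explain why they chose a two-way scale for patients who may be too impaired to test. This stands in part. It makes GOSE an indirect and coarse proxy, and a reasonable primary endpoint. But a reason for handling untestable patients does not show that the scale isolates cognition, and a two-class global outcome cannot attribute a difference to it.

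Two stronger readings are tempting and should not be drawn. A reader might infer that no result of this trial could support any of its hypotheses. The documents do not support that, because the functional and hemodynamic hypotheses have matching endpoints. A reader might also infer that no cognitive data are collected at all. Neuropsychologists are mentioned and the schedule in Fig. 1 is not shown, so the supportable statement is that none is listed as an instrument, outcome or analysis. Condensation of a fuller protocol is an unlikely explanation for a missing cognitive endpoint, since the article sets out its instruments, outcomes and tests explicitly.

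**Conclusion.** The point holds as an inconsistency between what the trial says it tests and what it tests. The title, abstract hypothesis (1), abstract Discussion, study purpose and Discussion objective name cognition; the primary hypothesis, endpoint, sample size and test name functional outcome on dichotomized GOSE. On the listed outcomes, neither a positive nor a null primary result supports a conclusion about cognition.

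Its size is a matter of what may be claimed: one of the three stated hypotheses has no direct endpoint. Randomization, data collection, the sample size of 32 and the primary test are unaffected by this point. It should be corrected before results are interpreted, but it does not make the primary analysis unusable. The verdict rests on taking the article's outcome and instrument lists as complete, and on reading both severe-disability levels as unfavorable.

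**What to change.** Restate hypothesis (1), the study purpose and the Discussion objective so that they agree with Primary outcome measures: transcranial LED therapy, compared with sham, increases the proportion of patients with favorable GOSE at 3 months after the first stimulation. Add one sentence saying that the trial does not directly test cognition and that GOSE reflects it only indirectly.

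If the neuropsychologists named under Randomization and blinding already collect test data, list the tests and their time points as a secondary or exploratory outcome, with a rule set in advance for patients who have died or cannot be tested. If they collect none, nothing needs to be added.

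The cost is a narrower claim. The restatement needs no extra patients or visits and no change to the treatment or the primary analysis.

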**Discussion:**

This study evaluates early and delayed effects of TCLT on the cognitive rehabilitation for DAI following severe acute TBI. There is a paucity of studies regarding the use of this therapy for cognitive improvement in TBI. There are some experimental studies and case series presenting interesting results for TBI cognitive improvement but no clinical trials.

**Trial registration:**

ClinicalTrials.gov, NCT03281759. Registered on 13 September 2017.

**Electronic supplementary material:**

The online version of this article (10.1186/s13063-018-2632-5) contains supplementary material, which is available to authorized users.

## Background

Annually, there are 50,000 deaths from traumatic brain injury (TBI) in the USA, and there are 235,000 hospitalizations from non-fatal TBI. Recently, there has been an increase of 14% of TBI cases presenting to the emergency department [1, 2].

Recent studies show that about 124,000 (43.1%) of TBI patients discharged from acute hospitalizations developed TBI-related long-term disability [3]. The definition of disability was focused on findings from a previous population-based study, which included considerable difficulty or inability to perform activities of daily living, the presence of a post-injury symptom preventing patients from doing things they intend to do, and poor cognitive and mental health levels on standard measures [4].

It is relevant to mention that these data are likely underestimated, as the data published are solely from hospitalizations only. Thus, they probably do not include TBI patients treated in other settings or for whom treatment was not sought [3].

### Radiological features of DAI and clinical presentation

Recent data accepted that diffuse axonal injury (DAI) is now one of the most common types of primary lesions in patients with severe head trauma [5]. DAI not accompanied by an intracranial mass lesion occurs in approximately 50% of patients with severe TBI and causes 35% of all TBI deaths [6].

Patients with DAI present with important impairment of consciousness from the moment of trauma [7]. DAI is the most common cause of persistent vegetative state and severe disability in TBI [8]. Damage to the reticular activating system is proportional to the level and duration of coma noted after DAI [6]. Autonomic dysfunction symptoms seen in DAI (such as temperature control and satiety center disorders) have been associated with injury to the hypothalamus, which controls these activities [6].

In the chronic phase, DAI in milder forms can lead to residual neuropsychiatric problems and cognitive deficits, including concentration difficulties, focal neurologic lesions, memory loss, decreased attention span, intellectual decline, psychiatric disturbances, headaches, and seizures [5]. These disability symptoms are known as post-concussion syndrome [9]. DAI should be suspected in all closed head injury patients with persistent and significant impairment of consciousness in the acute phase or residual neuropsychiatric deficits in the chronic phase [5].

Disability symptoms caused by brain lesions are not usually evident in structural computed tomography (CT) or magnetic resonance imaging (MRI) [10–13]. CT may show some petechial foci of hemorrhage in the acute phase, but it underestimates DAI extent because less than 20% of DAI lesions are hemorrhagic [5]. Other radiologic features which could be appear are as follows: (1) single or multiple small intraparenchymal hemorrhages in the cerebral hemispheres (<2 cm in diameter); (2) intraventricular hemorrhage; (3) hemorrhage in the corpus callosum; (4) small focal areas of hemorrhage adjacent to the third ventricle (<2 cm in diameter); (5) brain stem hemorrhage [14]. Intraventricular hemorrhage arises from disruption of the subependymal plexus of the capillaries and veins that lie along the ventricular surface of the septum pellucidum, fornix, and corpus callosum [15].

DAI is caused by shearing forces which transect small blood vessels running in parallel with axons, leading to detectable microscopic hemorrhages. Gradient echo and T2*-weighted MR images detect signal dropout provoked by ion-containing heme groups in slow-moving blood [16]. MRI is more sensitive in the identification of shearing injuries because it enables detection of non-hemorrhagic as well as hemorrhagic lesions. The axoplasmic leakage and edema around areas of neuronal disruption in non-hemorrhagic lesions are more conspicuous on T2-weighted images [5]. Diffusion tensor imaging (DTI) MRI scans can show DAI signs [12, 17]. DTI is sensitive to detect water diffusion in the brain, presenting microstructural lesions in white matter tracts [18].

There are five white matter regions of interest where one can usually see the lesions:Anterior corona radiata (41% of TBI cases)Uncinate fasciculus (29% of TBI cases)Genu of the corpus callosum (21% of TBI cases)Inferior longitudinal fasciculus (21% of TBI cases)Cingulum bundle (18% of TBI cases) [19]

The loss of connectivity in the aforementioned tracts (DAI) is responsible for all the symptoms and signs of disability following TBI [11].

### Principles of transcranial red/NIR LED photobiomodulation

The use of red or near-infrared (NIR) light to stimulate or regenerate tissue is called photobiomodulation. Trying to repeat an experiment performed in Boston, USA, the Hungarian Endre Mester accidentally discovered this process. He tried to use laser beams to destroy cancer cells experimentally implanted into a laboratory rat [20]. His mistake was to build a ruby laser that was only a tiny fraction of the power of the laser that had previously been used in Boston by McGuff [21]. Thus, he noticed that hair had regrown and wound had healed in the stimulated area where the tumor had been implanted [20].

Sometime after that, about 30 years ago, cadaver studies showed that NIR wavelengths (800–900 nm) and red (600 nm) could penetrate through the scalp and skull (about 2–3% of them can penetrate 1 cm from the cortex) [22, 23]. They also have the potential to improve the subnormal cellular activity of compromised brain tissue.

Photobiomodulation is a therapeutic tool for hypoxic, infected, and ischemic wounds. It also shows effectiveness in healing, reducing edema and inflammation, relieving pain, treating chronic inflammation and autoimmune diseases, recovery from ischemic heart disease, and attenuating degeneration of the optic nerve [24, 25]. Multiple studies testing its effects in TBI are in course [10, 20, 26, 27].

Wavelengths within the far-red to the near-infrared range (630–1000 nm) along with a minimal energy density of 4 J/cm^2^ are the optimal therapeutic intervention [28]. Stimulating biological processes proved to be effective with these wavelengths and energy density. It is believed that they act by four main actions:Stimulating mitochondria to increase adenosine triphosphate (ATP) production [29, 30] through increased cytochrome c oxidase (CCO) effect. CCO acts by absorbing light photon and avoiding nitric oxide (NO) inhibitory effect on itself. Thus, there is an increase in mitochondrial membrane potential, providing more oxygen consumption, as soon as more glucose is metabolized, and more ATP is produced [29].Inhibition of microglial activation and also acting as a strong antioxidant promoting an anti-inflammatory effect (increase in mitochondrial superoxide dismutase) [31, 32].Increasing regional cerebral blood flow [26, 33].Changing protein expression through signaling mediators and activation of transcription factors. These changes last for some considerable time and explain the long-lasting effect [21].Promoting *neurogenesis* and *synaptogenesis*. However, this was only seen in studies with small animals treated with NIR in the acute stage post-TBI [27, 32, 34].

Neurogenesis is the denomination given to the process of differentiation of a progenitor cell into a neuron. The subventricular zone and hippocampus are the areas where this process usually occurs. Another interesting fact is that it is not such a rare event in the brain as we once thought [35]. Synaptogenesis is a process of formation of new synapses. It is one of the brain recovery mechanisms after TBI [36].

Current small studies with acute severe TBI mice used transcranial NIR photobiomodulation to treat them. These studies have supported the notion that transcranial photobiomodulation increases neurogenesis and synaptogenesis. The protocol began 4 h post-TBI, and they discovered that there was significantly better recovery at 28 days post-TBI in mice receiving three daily transcranial NIR photobiomodulation treatments when compared to controls. The neurogenesis was notedly increased when measured by immunofluorescence staining of brain sections [37, 38].

The estimated mean of NIR light penetration depth through the scalp and skull is 23.6 ± 0.7 mm [39–41]. Considering the different areas of the skull, the percentage of penetration also changes (0.9% at the temporal region, 2.1% at the frontal region, and 11.7% at the occipital region) [42]. Transcranial photobiomodulation application is easier in the forehead, because of the absence of hair and longer wavelength, which facilitates NIR light penetration [20].

